### **Evaluation of clinical laboratory results**

Laboratory data will be summarized according to the type of laboratory examination.

The normal range and abnormal meaningful criteria will be referenced in the summary of laboratory data.

Changes compared to baseline will be analyzed using a pre- and post-treatment cross-table.

### **Vital signs**

The mean, standard deviation, median, minimum, and maximum of axillary body temperature, pulse, and decubitus blood pressure (systolic and diastolic blood pressure), as well as changes from baseline, were calculated at each specified follow-up time point.

### **Pharmacokinetic analysis**

C-T linear and semilog plots were drawn using the blood concentration (C) - time (t) data of each subject. At the same time, blood drug concentration at each time point was statistically described, including the number of cases, geometric mean, coefficient of variation, minimum and maximum.

Pharmacokinetic parameters of each subject were calculated, including Tmax, Cmax, AUC0-T, AUC0-∞, Vd, Kel, T1/2, CL and MRT. Statistical description of pharmacokinetic parameters of different dose groups and experimental and control groups, including number of cases, geometric mean, coefficient of variation, geometric coefficient of variation, minimum and maximum, etc.

### **Pharmacodynamics analysis**

Pharmacodynamics indexes were described by mean, standard deviation, maximum, minimum and median, and compared with the basic value in screening period. Paired T test was used to compare the differences before and after treatment in groups.

The groups were compared using a least square mean of the difference from baseline (with baseline as a covariable) and a 95% confidence interval.

The mixed effect model was used to analyze the change of acupuncture pain intensity at different time points after

administration compared with that before administration. The model took the change value of pain intensity at different time points in different administration areas compared with baseline as the dependent variable, and the pain intensity before administration as the covariable. Group (experimental group, control group), administration area/blank area, visit site, and interaction between group and visit site were fixed effects and individual factors were considered.

According to the model, the mean value of change in pain intensity at different time points of administration from baseline and its 95% confidence interval were calculated, as well as the mean value of difference between the experimental group and the control group and its 95% confidence interval.

Similar methods were used to analyze the range of analgesia.

Kaplan-meier method was used to statistically analyze the onset time and maintenance time of analgesia, and the median, Q1, Q3 and 95% confidence interval of the onset time and maintenance time of analgesia were calculated.

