**Table 1: Dose escalation protocol for single dose trials in healthy subjects**

| array | Dose (mg) | Number of healthy subjects (n)    |                                     |
|-------|-----------|-----------------------------------|-------------------------------------|
|       |           | Experimental group                | Control group                       |
|       |           | long-acting ropivacaine injection | ropivacaine hydrochloride injection |
| A     | 150       | 6                                 | 3                                   |
| B     | 230       | 8                                 | --                                  |
| C     | 300       | 8                                 | --                                  |
| D     | 350       | 8                                 | --                                  |
| E     | 400       | 8                                 | --                                  |
| Total |           | 38                                | 3                                   |

Positive control was set for cohort A, and no positive control was set for other dose groups. The study began at the minimum dose, with each subject receiving only one dose and only one dose cohort at a time. Safety assessments were conducted on days 7 and 21 after dosing, and the next cohort/batch trial was determined based on the results. If no significant adverse effects were observed in the maximum dose cohort (400mg), dose-escalation was not continued.

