## Pharmacodynamics methods:

**Experimental design, (1) Analgesic range measurement (Experiment 1) :** After the single point of administration, pain points were determined in two directions (when the VAS value of the test point (n) 1cm away from the point of administration was  $\geq 4$ , The measurement can be terminated at (n+1) time point) at 15min, 30min, 45min $\pm$ 3min, 1h, 1.5h, 2h, 3h, 4h, 5h, 6h, 7h, 8h, 9h, 10h, 11h, 12h  $\pm$ 5min, respectively. The distance between pain point and drug administration point (R1, R2) was measured and recorded, and the analgesic range diameter D = (R1 + R2).

**(2) Analgesic maintenance time, onset time and acupuncture pain intensity were measured (Test 2):** the intensity of acupuncture pain was measured before and after 15min, 1h, 4h, 8h, 10h, 12h, 14h, 18h, 21h, 24h, 27h, 30h, 33h, 36h, 48h, 72h;

**Baseline pain measurement:** Before drug administration, visual analogue scale (VAS) was used to measure the pain pressure baseline value (g) of VAS=4,5,6 in the pain test area, repeated for 3 times, and average value was taken respectively, namely the baseline value;

**Acupuncture pain intensity measurement:** a baseline value of VAS=4 was applied to the blank area to remind subjects of the sensation; In the pain test area, the baseline VAS=4 pressure was applied to the area, and the subjects were asked to compare the feeling with the blank area, and the feeling was "weaker", "similar", "stronger"?

When it was "weaker", baseline pressure at VAS= 5,6 was successively given and the inquiry process was repeated. When VAS=6 pressure was applied, subjects felt weaker and did not continue to increase the pressure. When it was "similar", record the maximum pressure value applied at this time; When it was stronger, the maximum pressure of the previous application was recorded and the onset time of analgesia maintenance time and the intensity of acupuncture pain were counted.

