### **Pharmacodynamics index evaluation**

#### **Analgesic onset time:**

**Evaluation of analgesic onset time:** analgesic onset time was recorded as the time when the threshold of measured pain sensation was greater than the threshold of baseline pain sensation of the subject (i.e., baseline

VAS=4 average acupuncture pressure) when the pain sensation was measured after drug administration.

**Pain threshold:** the minimum stimulus intensity when the human body feels pain. Pain threshold usually refers to a stimulus intensity that can cause pain sensation in human body, which is generally divided into pain sensation threshold and pain tolerance threshold (the maximum stimulus intensity that human body can tolerate) .

**Duration of analgesia:** Effective analgesia refers to the pain threshold greater than the baseline pain threshold during pain measurement. Theoretically, the duration of analgesia is the difference between the effective start time and the effective end time of analgesia. However, in the actual operation of this study, real-time dynamic monitoring could not be achieved, so the duration of analgesia in this study was divided into minimum duration of analgesia and maximum duration of analgesia. The true value of analgesic duration was between the minimum duration and the maximum duration.

Minimum duration of analgesia = last time from measurement to effective analgesia - first time from measurement to effective analgesia

Maximum duration of analgesia = (last measured to effective analgesia +1) measurement time - first measured to effective analgesia time

**Table 3: Acupuncture pain intensity: The intensity of acupuncture pain in this study was divided into 3 levels as described in the table below:**

|              |                                                                                                                          |
|--------------|--------------------------------------------------------------------------------------------------------------------------|
| Three Grade  | Pain threshold was measured $\geq$ baseline VAS=6 acupuncture pressure                                                   |
| Second Grade | Baseline VAS=6 acupuncture pressure > threshold of pain sensation $\geq$ baseline VAS=5 acupuncture pressure             |
| First Grade  | Baseline VAS=5 acupuncture pressure value > threshold of pain sensation $\geq$ baseline VAS=4 acupuncture pressure value |

Analgesic range of injection site (Study 1);

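### Test 2's pain ladder cannot record a value below baseline, so zero mean change is the wrong no-effect reference for the within-group t-test and confidence interval

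*Protocol*

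**What the plan says.** **Measurement (Protocol, Pharmacodynamics methods, acupuncture pain intensity).** Before dosing, the pressures that give VAS 4, 5 and 6 are found for each subject; call them P4, P5 and P6. At each post-dose reading P4 is pressed on the blank area as a reminder. Then "In the pain test area, the baseline VAS=4 pressure was applied to the area", and the subject says whether it feels weaker, similar or stronger than the blank press.

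- Weaker: "baseline pressure at VAS= 5,6 was successively given and the inquiry process was repeated". The ladder stops at P6: "subjects felt weaker and did not continue to increase the pressure".
- Similar: the pressure just applied is recorded.
- Stronger: "When it was stronger, the maximum pressure of the previous application was recorded".

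**Grading (Table 3).** The lowest grade is "Baseline VAS=5 acupuncture pressure value > threshold of pain sensation", bounded below by the baseline VAS=4 pressure. No grade lies below it.

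**Analysis (Pharmacodynamics analysis).** "Paired T test was used to compare the differences before and after treatment in groups". From the mixed model, "the mean value of change in pain intensity at different time points of administration from baseline and its 95% confidence interval were calculated".

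**Control (text under Table 1).** "Positive control was set for cohort A, and no positive control was set for other dose groups".

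**The concern.** A before-after test against zero is valid only if, without any drug effect, errors in the two directions cancel. Here they cannot. A subject who by chance finds the test press weaker moves up the ladder and may be recorded as having a raised threshold. A subject who by chance finds it stronger, or whose injection site is truly tender (tenderness is among the listed local reactions), has no lower value to be given.

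At 230 to 400 mg there is no control arm, so the before-after comparison is the only comparison with an untreated state within those cohorts. The control group has 3 subjects, all in cohort A. Onset, duration and intensity of analgesia are secondary objectives meant to inform the spacing of doses, so a result tilted towards efficacy could carry into later design.

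**Working it through.** The protocol states no alpha, power or expected effect for these tests, so there is no figure of its own to reproduce. A two-sided 5% level is assumed, to match the 95% interval. That is 2.5% in the direction of analgesia.

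**Step 1. Possible recorded values.**

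| Answers | Recorded | Change |
|---|---|---|
| similar at P4 | P4 | 0 |
| stronger at P4 | P4 (the blank-area press), or empty | 0 or missing |
| weaker, then stronger at P5 | P4 | 0 |
| weaker, then similar at P5 | P5 | P5−P4 > 0 |
| weaker, weaker, then stronger at P6 | P5 | P5−P4 > 0 |
| weaker, weaker, then similar or weaker at P6 | P6 | P6−P4 > 0 |

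The section on missing data says none will be processed, so an empty entry simply drops out.

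**Step 2. Mean change without a drug effect.** E(change) = Pr(P5 recorded)×(P5−P4) + Pr(P6 recorded)×(P6−P4). This is zero only if no reading ever rises by chance.

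**Step 3. One reading per subject, exact.** Score a rise as 1 and no rise as 0. With k rises among n subjects the paired t statistic is t = √[k(n−1)/(n−k)].

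- n=8: k=3 gives √(21/5)=2.05 (not significant); k=4 gives √7=2.65, p=0.033.
- n=6: k=4 gives √10=3.16, p=0.025.

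For n=8 the false-positive rate is Pr(Binomial(8,π) ≥ 4), where π is the chance that an inert site records a rise:

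| π | 0.10 | 0.15 | 0.20 | 0.25 | 0.30 |
|---|---|---|---|---|---|
| rate | 0.5% | 2.1% | 5.6% | 11.4% | 19.4% |

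All of these rejections point to analgesia. The rate passes 2.5% at π=0.157.

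**Step 4. Six areas averaged, n=8, one time point, simulated inert injection.** Assumptions not in the protocol: normal noise of SD s on each press, 'similar' means within 0.5 VAS of the blank press, equal pressure steps, independent test presses. The protocol does not say how often the blank press is repeated, so it is varied. Repeat runs agree within one or two percentage points.

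| Blank press | s=0.5 | s=1.0 |
|---|---|---|
| fresh for each area | 61% | 90–91% |
| repeated before every ladder step | 18% | 69% |
| one shared by all six areas | 10% | 27–28% |
| free of noise | 2% | 49% |

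The chance of a false rise per reading is about 11% (s=0.5) or 21% (s=1.0) with a noisy blank press, and 2.5% or 9.5% with a noise-free one. With one area per subject and n=8, rejection is 0 to 6% throughout.

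**Step 5. Checks.** Scoring the first answer as +1, 0 or −1 and testing that gives about 5% or below, at most 7.5%, in the settings run. For the 6-against-3 contrast of cohort A with both arms inert and the ladder unchanged, two-sided rejection is 4.5% to 4.8%, because both arms share the floor.

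**The case against.** - **Noise and averaging are not given.** This stands. The table runs from 2% to 61% at a single noise SD, so no one percentage can be claimed.
- **The most extreme settings are not the stated analysis.** This stands too. A reader might infer that an inert injection would nearly always be declared effective: averaging one area over 15 times gives 97% at s=0.5, and pooling all 38 test-drug subjects gives about 62% even with one reading each. The protocol states neither that averaging nor that pooling; it speaks of change at each time point.
- **Negative changes may be possible.** Pharmacodynamics analysis opens by comparing with a value from the screening period, and Table 10 lists a separate pain test on days −14 to −2. If that test were the comparator, changes could be negative. But the methods section takes baseline before administration, and the mixed model uses pain intensity before administration. The pre-dose reading is the better supported one; the wording still needs to be reconciled.
- **The mixed model has a blank-area term.** It does, but the Test 2 procedure limits intensity measurement to circles 1 and 2, both dosed, and the blank area receives only the reminder press. No blank-area ladder exists to absorb the noise.
- **The model also compares groups.** A reader might infer that the floor undermines every pharmacodynamic comparison. It does not: the concurrent contrast in cohort A is largely unaffected.
- **The outcome is secondary and escalation rests on safety.** Correct. No escalation decision turns on this test, which limits the weight of the point.
- **A three-level first answer loses intensity.** Correct if it replaced the pressure everywhere, which is why the fix confines it to the before-after test.

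**Conclusion.** The point holds, on the condition that baseline is the pre-dose value. The direction is certain from the text: recorded change is zero or positive, so the paired t-test and within-group interval have the wrong reference, and any false finding favours efficacy. Strictly, the hypothesis tested is no analgesia and no upward response error.

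The size is not certain. With one area at one time and n=8 the test is conservative or near nominal. With six areas averaged it may be anywhere from harmless to badly inflated, depending on noise and on how the blank press is repeated. The consequence falls mainly on cohorts B to E (4×8=32 of 38 test-drug subjects). The change should be made, but it does not threaten the safety or pharmacokinetic objectives.

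**What to change.** 1. Record the first-step answer (weaker, similar, stronger) at every reading, and do not store a first-step 'stronger' as the baseline pressure.
2. For the before-after test in each dose group, replace the paired t-test against zero by a sign or signed-rank test of weaker against stronger, with one summary per subject and time point.
3. Keep the pressure reached and Grades 1 to 3 for describing intensity and for the test-versus-control model, so that the VAS=5 and VAS=6 levels are not lost.
4. Report the within-group confidence interval for mean change as descriptive, with a note on the floor.
5. State that baseline is the pre-dose value of Pharmacodynamics methods, and reconcile this with the screening-period value in Pharmacodynamics analysis.

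**Cost.** One eCRF code for an answer already asked, plus analysis wording; no extra procedure or subject. The within-group result on a secondary endpoint will look less favourable. A sign test on few subjects is also coarse: with ties dropped, significance needs at least 6 subjects all in one direction (2×0.5⁶=0.031). Onset and duration, which count any recorded rise as analgesia, are not repaired by this change and should carry the same note.

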### **Adverse events**

Any subject receiving the investigational drug should be assessed for safety. The evaluation period shall be from the time of receiving the investigational drug to 21 days after the end of study or administration. AEs or SAEs occurring during this period shall be followed until they return to normal or stable (except for subjects who are dead, lost to follow-up, or have withdrawn their informed consent).

Adverse events were coded using MedDRA.

In this study, the adverse events (TEAE) occurred during treatment were mainly analyzed statistically. The adverse events occurred during the screening period to before the first administration were listed, but the statistical analysis of adverse events was not included.

Adverse events referred to below refer to adverse events occurring during treatment.

The incidence, number and incidence of all adverse events, drug related adverse events, serious adverse events and abortion related adverse events in each group were calculated.

According to systematic organ classification (SOC) and preferred term (PT) classification, the number of adverse events, the number of cases and the incidence of adverse events in the two groups were calculated.

A list of adverse events related to the study drug during treatment, a list of all adverse events, a list of adverse events resulting in shedding, and a list of serious adverse events were listed separately.

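### The pain-intensity model has a two-level group factor and no dose term, so on its plain reading it compares five pooled depot doses with a control that exists only in the 150 mg cohort

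*Protocol*

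**What the plan says.** The Protocol, under Pharmacodynamics analysis, takes "the change value of pain intensity at different time points in different administration areas compared with baseline as the dependent variable", adjusts for the pre-administration value and lists the fixed effects: "Group (experimental group, control group), administration area/blank area, visit site, and interaction between group and visit site were fixed effects". I read visit site as time point. From this model it reports "the mean value of difference between the experimental group and the control group and its 95% confidence interval". The section then adds: "Similar methods were used to analyze the range of analgesia".

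On where the control sits, the text below Table 1 states: "Positive control was set for cohort A, and no positive control was set for other dose groups". Table 1 has one experimental column, totalling 38 over five doses, and one control column, totalling 3. The Randomization section allocates subjects between the two drugs only within cohort A. The pharmacodynamic set (Analysis of the crowd) takes every dosed subject with post-dose data, from any cohort.

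For adverse events by organ class and preferred term, the statistical Adverse events section says that "the number of adverse events, the number of cases and the incidence of adverse events in the two groups were calculated".

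**The concern.** The protocol itself fixes the model terms, so this is not a detail left to an analysis plan. With a two-level group factor and no dose term, subjects given 150, 230, 300, 350 and 400 mg of depot share one mean. That mean is set against three control subjects who belong to the 150 mg cohort. The result cannot be read as a drug effect, because the depot subjects differ from the controls in dose, cohort and calendar time as well as in drug. The model also gives no estimate by dose.

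Three further statements have related faults. The area factor has a blank level that the measurement sections do not appear to fill. The analgesic-range analysis borrows a group comparison for a test with no control group. The organ-class adverse event table has two columns, although the first main objective is safety and tolerability at different doses.

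**Working it through.** **Plan's own count.** Table 1: 6 + 8 + 8 + 8 + 8 = 38 experimental; 38 + 3 = 41. This reproduces the 41 subjects stated under Study design.

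**Mean depot dose if all cohorts are pooled.** (6×150 + 8×230 + 8×300 + 8×350 + 8×400)/38 = (900 + 1840 + 2400 + 2800 + 3200)/38 = 11140/38 = 293.2 mg. That is 293.2/150 = 1.95 times the dose of the only controlled cohort.

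**Share without a randomised control.** Cohorts B to E: 32/38 = 84.2%. Cohort A: 6/38 = 15.8%.

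**Possible size of the confounding.** The protocol gives no dose-response slope, so this is an assumption. Suppose the two drugs are equal at 150 mg and response rises linearly by s outcome units per 100 mg. The pooled contrast is then s × (293.2 − 150)/100 = 1.43s instead of 0:

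| s per 100 mg (assumed) | Pooled contrast | Cohort A contrast |
|---|---|---|
| 0.10 | 0.14 | 0 |
| 0.25 | 0.36 | 0 |
| 0.50 | 0.72 | 0 |

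**What pooling buys.** Assume one value per subject and a common SD. The standard error of the difference is SD × √(1/n₁ + 1/n₂).

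- Pooled, 38 v 3: √(1/38 + 1/3) = 0.600 SD. With 41 − 2 = 39 df, the 95% half-width is 2.023 × 0.600 = 1.21 SD.
- Cohort A contrast within a six-level factor, 6 v 3: √(1/6 + 1/3) = 0.707 SD. With 41 − 6 = 35 df, the half-width is 2.030 × 0.7071 = 1.44 SD.
- Cohort A analysed alone, 6 v 3: 0.707 SD. With 9 − 2 = 7 df, the half-width is 2.365 × 0.707 = 1.67 SD.

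The three controls dominate the standard error, so adding 32 depot subjects lowers it only from 0.707 to 0.600 SD.

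**Blank area.** The model has an administration/blank factor. The Test 2 method section (safety, tolerability and pharmacokinetics of a single subcutaneous dose) confines pain-intensity measurement to circles 1 and 2, and the blank region is a separate, fourth area. Pharmacodynamics methods gives the blank region another role: "a baseline value of VAS=4 was applied to the blank area to remind subjects of the sensation". On those two sections the blank level has no outcome data and its effect cannot be estimated.

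**Analgesic range.** Range is measured only in Test 1. That test has 3 subjects, all given the test drug, and range measurements only after dosing. The Statistical analysis section calls for descriptive analysis of it. A group effect and a change from baseline cannot be fitted there.

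**The case against.** The strongest reply is that pooling is never stated. The Randomization and Blinded design sections use the experimental/control split for cohort A, and the neighbouring Pharmacokinetic analysis section names dose groups and the experimental/control comparison as two separate things. The drafters may therefore have meant a cohort A comparison. This stands as a possible reading. It does not settle the matter: the model section states no such limit, Table 1 applies the experimental heading to all 38, and the analysis set is unrestricted. If cohort A was meant, the model covers 9 of 41 subjects and leaves out cohorts B to E.

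It is also fair that pharmacodynamics is a secondary purpose, that escalation is decided on safety, and that no decision rule uses this contrast. Least-squares mean comparisons of the groups are planned elsewhere in the section without a limit to two. For adverse events, overall incidence is by each group and full listings are required, so a dose relation could be recovered; only the organ-class table is affected.

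A reader might go further on two points that the documents do not support:

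- *Untreated skin shrinks the estimated effect.* That would require blank-area outcomes to enter the model without area interactions. The measurement sections indicate that there are none, so what is shown is a contradiction, not dilution.
- *The baseline is wrong*, because indices are "compared with the basic value in screening period". Under Trial period, screening runs to day −1, and Table 10 schedules needling pain on that day. The mixed model in any case uses the pre-administration value.

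**Conclusion.** The concern holds on the plain reading of the text. The specified contrast sets a depot group with mean dose 293 mg, 84% of it never randomised against control, against three subjects in the 150 mg cohort. It confounds drug with dose and cohort. The protocol does not say outright that doses are pooled, so it would be too strong to call the comparison invalid under every reading. A cohort A fit would be a randomised, though very imprecise, 6 v 3 comparison. The numerical size of the confounding depends on an assumed slope.

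The blank-area level conflicts with the measurement sections, and the range model cannot be applied to Test 1; neither point depends on the pooling question. The two-group organ-class table does not show adverse events by dose.

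The effect is on a secondary comparison and on one safety tabulation, not on the pharmacokinetic aims or on escalation. It should be fixed before analysis.

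**What to change.** - Replace the group factor with a treatment-by-dose factor: control, and depot 150, 230, 300, 350 and 400 mg.
- Report depot v control as the randomised contrast within cohort A (6 v 3). Report comparisons across doses separately, labelled non-randomised.
- Remove the blank level from the area factor. If blank-area outcomes are in fact recorded, say so in the measurement sections, add group-by-area and area-by-visit terms, and report the contrast for treated skin.
- Delete the model for analgesic range and keep the descriptive summary.
- Tabulate adverse events by organ class and preferred term for each dose group and for control.

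The cost is wording and a wider interval for the drug comparison: a half-width of about 1.44 SD with the six-level factor, or 1.67 SD from cohort A alone, instead of 1.21 SD. The 1.44 figure takes its residual variance from all cohorts and so assumes equal variance across doses. All three figures come from the simple one-value-per-subject calculation; repeated measurements within a subject would change them.
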